### Statistical methods

#### Sample size calculation

According to the study of Kruizenga et al. [10], 412 patients per arm (a total of 824 patients for this study) are required to detect a difference in hospital stay of 2.6 days, assuming a standard deviation of 8 days in the intervention group and 13.3 days in the control group. Calculations were performed considering a two-tailed power of 90%, an alpha of 0.05, and 10% of potential losses.

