#### Cost-effectiveness analysis

We will analyze the cost and cost-effectiveness of implementing the malnutrition screening tool CIPA versus standard practice in patients admitted to the Internal Medicine and General and Digestive Surgery wards. These analyses will be in line with accepted economic evaluation methods.

The cost will be assessed from a National Health Service perspective and, therefore, only include medical costs incurred by the health care service. Based on data from the hospital as well as the national sources, we will assign a unit cost to each component of health care utilization collected in this trial.

The cost-effectiveness measure will be the incremental cost per quality-adjusted life year (QALY) gained. QALYs will be calculated based on the HRQoL and mortality data collected during the trial. Patient-specific utility profiles will be created assuming a straight-line relation between all patients’ EQ-5D-5 L scores from either follow-up point. The QALYs experienced by each patient from baseline to 3 months will be calculated as the area underneath this profile. We will investigate differences in baseline characteristics and, if necessary, use regression methods to control for them.

Cost-effectiveness will be summarized as the incremental cost-effectiveness ratio (ICER) by dividing the estimated differences in cost by the differences in QALYs. Non-parametric methods to calculate confidence intervals around the ICER, based on bootstrapped estimates of the mean cost and QALY differences, will be used. Further, the bootstrap replications will be used to create a cost-effectiveness acceptability curve, which will reveal the probability that each alternative is cost effective for different values of willingness to pay for an additional QALY. We will also subject the results to extensive, deterministic (one, two-, and multi-way) sensitivity analyses.

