## Discussion

This research project evaluates the effectiveness and cost-effectiveness of implementing a hospital nutrition screening (in this case the CIPA method) in a detailed manner, comprising a large number of variables to analyze the effect of its introduction from different perspectives. On the one hand, clinical variables, such as medical complications during the admission process, mean length of stay, mortality, readmission, or even patient-directed procedures are assessed. On the other hand, data collection includes costs of the visits from dietitians and other skilled health personnel, as well as the costs of nutrition support, not only ONS, but also tube feeding or parenteral feeding, where necessary.

Disease-associated malnutrition is a perfect target for screening due to its high prevalence and the established therapeutic measures that can mitigate its deleterious effects when applied timely, thereby allowing clinical and economic improvement [18–22]. However, there is no ideal method of nutrition screening, as those that best predict the patient’s clinical course are the most complex to perform and require substantial efforts for implementation in hospitals with many patients, as e.g., SGA [7] or NRS2002 [6], while others that are easier and more feasible to carry out, do not predict that course so well. Consequently, the ideal screening system should adapt to the hospital characteristics, predict patient outcome, be workable by most caregivers, and should be inexpensive and not time-consuming [23–25].

The CIPA screening meets all these criteria: (1) it employs tools used in everyday clinical practice that do not require specialized personnel; (2) it is quick to perform; (3) it is objective; (4) it is inexpensive, since the only extra cost is the general determination of serum albumin at hospital admission, which is negligible for a measure with foreseeable, significant savings; (5) it is able to predict the patients’ prognosis, as in a study in 221 non-surgical patients the CIPA screening detected patients with a comparably longer mean length of stay of one week and a higher mortality, similar to the findings of another early study that allowed its development [13, 14].

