It is worth noting that the SNHS only covers the cost of post-discharge nutrition supplements under very specific conditions, e.g., in cancer patients, patients with dysphagia, neurodegenerative diseases, and similar. Consequently, many of the patients who need nutrition support in hospital would not be able to continue after their discharge. For this reason, the number of patients with continued nutrition supplementation after discharge is expected to be rather low in this study.

At the same time, due to training and greater awareness about diagnosis and treatment of malnutrition among the clinical staff of the HUNSC, particularly in the surgical wards, the number of patients excluded for having nutritional support before finalizing the CIPA screening has been higher than expected, which led to an extension of the recruitment period.

Therefore, with the scientific rationale in favor of a nutrition management of malnourished patients and with tools for early detection of this condition at hand, it is foreseeable that the implementation of a cheap and simple hospital nutrition screening results in a cost-effective intervention. However, properly designed and methodologically unbiased studies are required to evaluate this relationship. Given the scarcity of literature in regard to this type of evaluations, we hope to fill the evidence gap between hospital nutrition screening and health care cost savings with this study, and, if proven cost effective, promote the universal implementation of the CIPA screening system in hospitals through appropriate political strategies.

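### The planned bootstrap confidence interval around the ICER may be hard or impossible to interpret in the scenario the protocol itself anticipates; net monetary benefit from the same replicates avoids this (minor)

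*Protocol article*

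**What the plan says.** The Cost-effectiveness analysis section of the protocol article defines the summary measure: "Cost-effectiveness will be summarized as the incremental cost-effectiveness ratio (ICER) by dividing the estimated differences in cost by the differences in QALYs". For its uncertainty it commits to an interval on that ratio: "Non-parametric methods to calculate confidence intervals around the ICER, based on bootstrapped estimates of the mean cost and QALY differences, will be used". It adds that "the bootstrap replications will be used to create a cost-effectiveness acceptability curve", followed by deterministic sensitivity analyses. The horizon is short: "The QALYs experienced by each patient from baseline to 3 months will be calculated as the area underneath this profile". The section mentions neither net monetary benefit nor the cost-effectiveness plane.

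On the expected result, the Discussion calls the extra cost of the screening "negligible for a measure with foreseeable, significant savings" and concludes that "it is foreseeable that the implementation of a cheap and simple hospital nutrition screening results in a cost-effective intervention". The Sample size calculation section says that "412 patients per arm (a total of 824 patients for this study) are required to detect a difference in hospital stay of 2.6 days". The article states no expected QALY gain, utility SD, cost difference or cost SD.

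**The concern.** A confidence interval for a ratio is useful only if larger and smaller values of the ratio mean better and worse. For an ICER this holds within a quadrant where there is a trade-off (dearer and better, or cheaper and worse). It fails in two situations that matter here.

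- **Dominance.** If the intervention saves money and improves QALYs, the ICER is negative, and its size does not reflect merit. Choosing another type of bootstrap interval does not cure this, because the quantity itself is unordered.
- **A denominator near zero.** If some replicates have a negative QALY difference, ratios from opposite quadrants share a sign and cannot be ranked together. The limits can then run to very large values in both directions.

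Cost-effectiveness is part of the trial's stated aim, so this interval would be a prominent output. At stake is whether readers can use it; the data and the estimates are not in question.

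**Working it through.** **1. The plan's own figure and the analysed number.** Inputs from the Sample size calculation section: difference 2.6 days, SDs 8 and 13.3, two-sided alpha 0.05, power 90%, losses 10%.

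n per arm = (8² + 13.3²) × (1.960 + 1.282)² / 2.6² = 374.4, and 374.4 × 1.10 = 411.9, which reproduces 412. Taking 10% losses from 412 leaves 412 × 0.90 = 370.8, so 371 per arm is used below.

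**2. Direction of the cost difference under the design assumptions.** SE of the difference in stay = √[(8² + 13.3²)/371] = 0.81 day, and 2.6/0.81 is about 3.2. About 99.9% of replicates would show a shorter stay. If bed-day savings exceed the cost of screening and treatment, as the Discussion expects, the numerator is negative. The ICER is then negative whenever QALYs improve.

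**3. Ordering of negative ICERs.** This step needs no assumption about the true size of the QALY gain. The values are illustrative; 20,000 per QALY is an assumed willingness to pay.

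| Saving | QALY gain | ICER | Net benefit at 20,000 |
|---|---|---|---|
| 300 | 0.010 | -30,000 | 20,000 × 0.010 + 300 = 500 |
| 300 | 0.004 | -75,000 | 20,000 × 0.004 + 300 = 380 |

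The worse result has the more negative ICER. Yet raising the saving at a fixed gain also makes the ICER more negative, and that is an improvement. Net benefit ranks the results correctly.

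**4. Zero crossing of the denominator.** Assumption: SD of 3-month QALYs 0.05 to 0.10. SE = SD × √(2/371) = 0.0037 to 0.0073. Share of replicates with a negative denominator = Φ(-gain/SE).

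| True QALY gain | SD 0.05 | SD 0.10 |
|---|---|---|
| 0.002 | 29% | 39% |
| 0.005 | 9% | 25% |
| 0.010 | 0.3% | 9% |

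**5. What the interval could look like.** The cost and QALY inputs here are assumptions and are not in the document. Each case uses 200,000 simulated replicates with independent cost and QALY differences, and percentile limits.

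- *Case A:* saving 300, gain 0.004, cost SD 4,000, QALY SD 0.07. About 66% of replicates are cheaper and better, 19% cheaper and worse, 12% dearer and better, and 3% dearer and worse. The ICER interval is about -830,000 to +770,000; its limits vary by some tens of thousands between runs. Net benefit at 20,000 per QALY is about 380 (95% interval about -230 to 990).
- *Case B:* the 2.6-day design effect at 500 per bed day, 150 extra cost per patient, utility SD 0.25 over 0.25 year, mean utility gain 0.02 (0.005 QALY). 86% of replicates are dominant and 14% are cheaper with a QALY loss. The interval is about -2.3 million to +2.0 million.
- *Case C:* as B with a mean utility gain of 0.05 (0.0125 QALY). 99.5% of replicates are dominant. The interval stays negative, about -329,000 to -25,000, but its limits still cannot be ranked.

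**The case against.** Four points can be made for the plan.

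- **The small QALY gain is an inference.** A reader might conclude that the QALY difference can only be a few thousandths, so that the interval is bound to fail. The document does not support this. It states no expected gain, builds QALYs from both quality of life and mortality, and may count the hospital stay on top of the three months. With a gain of 0.010 the share of negative denominators is only 0.3-9%, and in Case C zero crossing practically disappears. This objection stands: zero crossing is possible, not established.
- **The acceptability curve is already planned.** It comes from the same replicates and is valid in all four quadrants, so decision uncertainty will be reported. This stands too and lowers the weight of the point. The curve does not, however, give the size of the net gain or an interval for it.
- **The text does not prescribe a percentile interval.** True, and the handling of quadrants may be set out in a fuller plan that is not shown. So the widths in step 5 illustrate one method. The ordering problem does not depend on the bootstrap variant, and the choice of the ICER as the quantity to be bounded is made in this text.
- **A wholly negative interval would simply be read as dominance.** Largely so, but then the statement of dominance is what informs the reader, and the limits add nothing that can be interpreted.

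**Conclusion.** The point holds as a minor one. If the trial gives the result its authors foresee, with savings and some QALY improvement, the ICER will be negative and its confidence limits will not order results by merit. This rests on the document's own expectations and on arithmetic.

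Zero crossing is a second and conditional problem. Under the assumed SD of 0.05 to 0.10 and 371 patients per arm it ranges from 0.3% of replicates (gain 0.010, smaller SD) to 39% (gain 0.002, larger SD). It would go too far to say that the interval will be uninterpretable whatever the result: if essentially all replicates were dearer and better, for example, an ICER interval would be usable. The primary endpoint, the cost and QALY estimates and the acceptability curve are unaffected.

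**What to change.** Amend the uncertainty paragraph of the cost-effectiveness analysis to report, from the bootstrap replicates already planned:

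- incremental net monetary benefit with a 95% interval, at the willingness-to-pay values used for the acceptability curve;
- mean differences in cost and in QALYs, each with its own interval;
- the replicates on the cost-effectiveness plane, beside the acceptability curve.

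Report an ICER and its interval only when the point estimate and essentially all replicates lie in a single trade-off quadrant. Otherwise state dominance or rely on net benefit.

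The cost is a change of wording and a few lines of analysis code, with no new data and no further resampling. The article describes data collection as still under way, with the analyses to follow, so the change can still be specified in advance.

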#### Duration of fieldwork

The recruitment phase lasted for 15 months. Patients are being followed up for three more months post-discharge. Thereafter, a subsequent phase of data cleansing, identification of unit costs, and data analyses will take place.

#### Monitoring

Trial monitoring is the responsibility of the research team in charge of all quality control activities, assessing adherence to the trial protocol, timely work plan execution, and comprehensiveness of data acquisition and data quality. The databases have been designed to avoid, for each variable, downloading of inappropriate values.

#### Trial status

This study is ongoing, the investigators are still collecting data.

## Discussion

This research project evaluates the effectiveness and cost-effectiveness of implementing a hospital nutrition screening (in this case the CIPA method) in a detailed manner, comprising a large number of variables to analyze the effect of its introduction from different perspectives. On the one hand, clinical variables, such as medical complications during the admission process, mean length of stay, mortality, readmission, or even patient-directed procedures are assessed. On the other hand, data collection includes costs of the visits from dietitians and other skilled health personnel, as well as the costs of nutrition support, not only ONS, but also tube feeding or parenteral feeding, where necessary.

Disease-associated malnutrition is a perfect target for screening due to its high prevalence and the established therapeutic measures that can mitigate its deleterious effects when applied timely, thereby allowing clinical and economic improvement [18–22]. However, there is no ideal method of nutrition screening, as those that best predict the patient’s clinical course are the most complex to perform and require substantial efforts for implementation in hospitals with many patients, as e.g., SGA [7] or NRS2002 [6], while others that are easier and more feasible to carry out, do not predict that course so well. Consequently, the ideal screening system should adapt to the hospital characteristics, predict patient outcome, be workable by most caregivers, and should be inexpensive and not time-consuming [23–25].

The CIPA screening meets all these criteria: (1) it employs tools used in everyday clinical practice that do not require specialized personnel; (2) it is quick to perform; (3) it is objective; (4) it is inexpensive, since the only extra cost is the general determination of serum albumin at hospital admission, which is negligible for a measure with foreseeable, significant savings; (5) it is able to predict the patients’ prognosis, as in a study in 221 non-surgical patients the CIPA screening detected patients with a comparably longer mean length of stay of one week and a higher mortality, similar to the findings of another early study that allowed its development [13, 14].

Ethical constraints on prospective studies of nutrition intervention in malnourished patients resulted in scientific evidence of the benefit of treating these patients primarily from retrospective studies. The outstanding work of Phillipson TJ et al. [20] revealed that treatment with ONS decreased the mean length of stay, readmission rate, and health cost. Likewise, two meta-analyses, recently published by Elia M et al., describe the clinical and economic benefits of ONS treatment in malnourished, in-hospital patients and community settings [21, 22]. Furthermore, a recently published, first prospective, randomized, double-blind study showed that a nutrition supplement decreases the incidence of mortality in in-hospital patients during their stay and up to 3 months post-discharge [23].

Using the SNAQ tool, a study by Kruizenga HM et al. [10] analyzed the cost-effectiveness of the implementation of a nutrition screening at hospital admission. The authors mainly evaluated the decrease in the mean stay as a measure to reduce costs, while taking into account extra expenses due to ONS treatment and dietitian visits, finding the tool to be cost effective primarily in the fragile patient.

Although a poor nutrition status relates to a limited HRQoL both in inpatients as well as non-institutionalized patients, very few studies have assessed HRQoL associated with the nutrition status or treatment in risk patients [26–28], most of them focusing on clinical parameters. The present study includes the analysis of the state of HRQoL by means of the EQ-5D-5 L questionnaire, not only as a generic reference in terms of the association of the nutrition status with the HRQoL, but also because QALYs are the most widely used measure to evaluate the cost-effectiveness of an intervention in the field of health care [29].

The limitations of the present study include the impossibility to perform a double-blind study, as the responsible doctor should know if the patient has screened positive or negative to act on their clinical criterion. In some instances, standard clinical practice may also cause delays in adapting the pattern of nutrition treatment to the screening result, and treatment might be overlooked at hospital discharge even when required by the patient.

It is worth noting that the SNHS only covers the cost of post-discharge nutrition supplements under very specific conditions, e.g., in cancer patients, patients with dysphagia, neurodegenerative diseases, and similar. Consequently, many of the patients who need nutrition support in hospital would not be able to continue after their discharge. For this reason, the number of patients with continued nutrition supplementation after discharge is expected to be rather low in this study.

At the same time, due to training and greater awareness about diagnosis and treatment of malnutrition among the clinical staff of the HUNSC, particularly in the surgical wards, the number of patients excluded for having nutritional support before finalizing the CIPA screening has been higher than expected, which led to an extension of the recruitment period.

Therefore, with the scientific rationale in favor of a nutrition management of malnourished patients and with tools for early detection of this condition at hand, it is foreseeable that the implementation of a cheap and simple hospital nutrition screening results in a cost-effective intervention. However, properly designed and methodologically unbiased studies are required to evaluate this relationship. Given the scarcity of literature in regard to this type of evaluations, we hope to fill the evidence gap between hospital nutrition screening and health care cost savings with this study, and, if proven cost effective, promote the universal implementation of the CIPA screening system in hospitals through appropriate political strategies.

## Abbreviations

BMI: Body mass index
CHADx: Classification of hospital-acquired diagnoses
CI: Charlson index
CIPA: Control of food intake, protein and anthropometry
CRF: Case report form
DRG: Diagnosis-related group
EMR: Electronic medical record
HM: Hospital malnutrition
HRQoL: Health-related quality of life
HUNSC: Hospital Universitario Nuestra Señora de Candelaria
ICD-10: International classification of diseases (10th revision)
ICER: Incremental cost-effectiveness ratio
MUAC: Mid-upper arm circumference
NRS2002: Nutritional risk screening 2002
ONS: Oral Nutrition supplements
QALYs: Quality-adjusted life years
SGA: Subjective global assessment
SNAQ: Short nutritional assessment questionnaire
SNHS: Spanish national health system
